#### Primary healthcare professionals

This study will involve GPs and pharmacists practicing in primary care, i.e., in medical practices or community pharmacies. GP and CPs in the Pays de Loire region will be contacted by e-mail through multiple channels like research networks and professional associations. An evening webinar regarding BZDR misuse will be held for physicians and pharmacists in the Region. The objective will be to raise awareness of the problem and to explain the study to professionals. If a GPs shows interest, he/she will be asked to reach out the pharmacist (or vice versa) in order to form a pair (cluster). Pre-existing interactions between healthcare professionals of the same area is a major driver regarding the optimal implementation of the intervention within the cluster. Moreover, as in the context of a pragmatic trial, this way of conducting recruitment is the most coherent regarding the evaluation of what would be observed in practice when deploying the intervention to a larger scale. If both GP and CP agrees to participate, signed informed consent will then be obtained, and the cluster will be randomized.

### Randomization

A schedule for enrollment, randomization and allocation, interventions, and assessments for the study is presented in Table 1. The randomization will be performed by cluster of GP-CP pairs in open without stratification with a ratio of 1:1 using the *Ennov clinical* software via a secure connection to the servers of the Nantes University Hospital. The information necessary for communication will be provided to the recruiting GPs by a data manager of the Nantes University Hospital. The randomization will be computer-generated by blocks of 6 as the clusters are recruited. The trial statistician and the researchers assessing the outcomes will be blinded to the randomization results.

**Table 1 tab1:** Schedule of enrollment, interventions, and assessments.

	2022	2023			2024		
	June-Dec.	Jan.-Feb.	March-Sept.	Oct.-Dec.	Jan.-March	April–June	July-Sept.
Enrollment							
Recruitment and GP-CP clusters forming	X	X	X				
Eligible patients’ identification			X				
Clusters allocation		X	X				
Intervention							
CP training in MI performing		X	X				
Patients enrollment and MI 1 to 3			X	X			
Monthly reports to GP			X	X	X		
Assessments							
Acceptability/Adoption		X	X				
Appropriateness (interviews)				X		X	
Cost						X	
Fidelity			X	X	X	X	
BZDR consumption				X	X		
Health-outcomes questionnaires				X	X		
Dissemination							X

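### A single fixed block size of 6 in an open, sequential, unstratified list weakens cluster-level allocation concealment: about 9 of 40 assignments are certain to anyone holding the allocation history

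*Protocol article*

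**What the plan says.** The Randomization section of the protocol article allocates "by cluster of GP-CP pairs in open without stratification with a ratio of 1:1" and adds: "The randomization will be computer-generated by blocks of 6 as the clusters are recruited". There is therefore one list for the whole trial, one block size, and allocation that proceeds as clusters arrive.

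The list is held centrally, in "software via a secure connection to the servers of the Nantes University Hospital". On communication, the section says: "The information necessary for communication will be provided to the recruiting GPs by a data manager of the Nantes University Hospital".

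Under Primary healthcare professionals, the GP and the pharmacist form the pair themselves after a general call. The order of events is then: "If both GP and CP agrees to participate, signed informed consent will then be obtained, and the cluster will be randomized".

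The Randomization section names the trial statistician and the outcome researchers as blinded, and the Limits section adds the clinical research officer. The Intervention section (Step 2) says that the sponsor's public health department will, if required, accompany intervention pharmacists in their first interviews. Neither that department nor the data manager is listed as blinded.

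**The concern.** In an open trial, each allocation can become known to staff once it is made. If the block size is constant and known, past allocations reveal future ones: once one arm has used its three places in a block, the rest of that block is determined. A person with this knowledge who also influences which pair is entered next could, even without intent, steer a keen pair towards one arm.

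The factor at risk is the motivation of the GP and the pharmacist. The Limits section itself expects participating professionals to be already convinced of deprescribing and relies on randomization as the answer. There are only 20 clusters per arm and no stratification. The covariates that the Statistical analysis section names as a minimum (age, sex, past attempts, suspected addiction) are all patient characteristics. The mixed model allows for correlation within clusters but does not correct an imbalance in cluster motivation between arms.

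**Working it through.** **Inputs.** Block size 6, ratio 1:1, one list (Randomization). 20 pairs per arm, so 40 clusters, with 10 patients each (Sample size and power).

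**The plan's own figure.** The article gives no figure for predictability. The 40 clusters come from its sample size, which reproduces. With a two-sided 5% level (assumed; sidedness is not stated), 80% power, 5% against 15%, and unpooled variance:

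- n per arm = (1.960 + 0.842)² × (0.05 × 0.95 + 0.15 × 0.85) / 0.10² = 137.4
- design effect = 1 + (10 − 1) × 0.05 = 1.45
- 137.4 × 1.45 = 199.2, against the stated 200.

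The point below does not affect this.

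**Certain assignments in a full block.** A 3:3 block has 6!/(3!·3!) = 20 equally likely orders. An assignment is certain once one arm has used its three places.

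| Position | 1 | 2 | 3 | 4 | 5 | 6 | Sum |
|---|---|---|---|---|---|---|---|
| P(certain) | 0 | 0 | 0 | 2/20 | 8/20 | 1 | 1.5 |
| P(best guess correct) | 0.5 | 0.6 | 0.6 | 0.7 | 0.7 | 1 | 4.1 |

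Per full block, 1.5/6 = 25% are certain and 4.1/6 = 68.3% are guessed correctly by naming the arm with more places left.

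**Over 40 clusters.** 40 = 6 × 6 + 4, so the last block stops at position 4.

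- Certain: 6 × 1.5 + 0.1 = 9.1, and 9.1/40 = 22.75%.
- Best guess: (6 × 4.1 + 2.4)/40 = 27/40 = 67.5%.

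**With varying block sizes.** Simulation of 40 clusters (3,000 runs). The observer knows every earlier allocation and the set of possible sizes, but not their order:

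| Block sizes | Certain | Best guess correct |
|---|---|---|
| fixed 6 | 22.7% | 67.5% |
| 4/6 | 5.6% | 68.9% |
| 4/6/8 | 2.2% | 67.6% |

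Out of 40 clusters, certain assignments fall from about 9 to about 2 (4/6) or about 1 (4/6/8). The best-guess rate does not improve.

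**Arm balance at 40 clusters.** Under the current rule, four places of a 3:3 block split 3:1 at worst, giving 18 + 3 = 21 against 18 + 1 = 19. With 4/6 the worst case is also 21:19. With 4/6/8, a final block of 8 cut after four places could split 4:0, giving 22:18.

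**The case against.** The strongest reply is that the informed observer is assumed. The 22.75% applies only to someone who knows the block size, the block boundaries and every earlier allocation in order, and it does harm only if that person also affects which pair enters next. The list sits in central software. Pairs form themselves, and both professionals sign before the cluster is randomized. A GP or pharmacist has no stated access to other clusters' results. The article also condenses a fuller protocol, which may restrict who sees the sequence. All of this stands, and silence on access to the sequence is not held against the article.

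A reader might infer that one hospital team randomizes, trains and supports the intervention pharmacists and so knows everything. The article does not say that: the motivational interviewing training is given by a certified organization, and the hospital's support is offered only where required. A reader might also infer that the block size was public while clusters were being allocated. Table 1 places allocation in January to September 2023, and nothing shows that the article was available then.

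The reply does not remove the stated rule itself. Central software hides the list but does not prevent inference from past allocations. Consent before randomization stops a pair from reacting to its own result, but it does not fix the order in which consented pairs are entered. Table 1 starts cluster formation in June 2022 and allocation in January 2023, so a pool of waiting pairs is plausible, though this is an inference.

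**Conclusion.** The point holds as a limited weakness. The constant block of 6 makes about 9 of the 40 planned assignments (22.75%) certain for a person with the block size and the ordered history. The sponsor's data manager and its public health department could learn allocations, and neither is listed as blinded, but the article does not show that either holds the full history or enters clusters.

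The stronger reading, that allocation is not concealed when clusters are enrolled, is not supported. More than three quarters of assignments remain uncertain even to a fully informed observer, and the central software and prior consent are real safeguards. No bias in the treatment effect can be quantified from the article, and the sample size is unaffected. This is a low-severity improvement that costs little.

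**What to change.** In the Randomization section, replace the fixed block of 6 with randomly varying block sizes, for example 4/6 or 4/6/8. State that the sizes are withheld from everyone who contacts, consents or enters clusters, and that clusters are entered strictly in order of signed consent. The last rule matters because varying sizes alone leave the best-guess rate near 68%.

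Optionally, randomize pairs that have already consented in batches, fixing the members of each batch before any of its allocations is generated. The batch should not wait for patient lists: Table 1 places identification of eligible patients from March 2023, after allocation and pharmacist training begin in January-February.

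The cost is a software parameter and one or two sentences. The arms may end one or two clusters away from 20 each (21:19 or 22:18 at worst for these sizes), and the current rule already allows 21:19. Batches would add a short wait for some pairs. If allocation is already complete, the report should instead state who knew the block size and the allocation history, and whether clusters were randomized in order of consent.

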### Intervention

Deprescribing will be implemented through 3 successive steps, the cornerstones of which are interprofessional collaboration between GPs and CPs, and training and methodological support for CPs.

#### Step 1: medical encounter with the GP and submission of documents

Patients in the GP-CP clusters randomized to the intervention arm will be offered a joint GP-CP deprescribing intervention by their GP. The physician will present the study schedule to the patients and inform them of the planned follow-ups.

#### Step 2: medication treatment dispensing and MI

Following the medical consultation, the patients will go to the pharmacy to get their medication treatment dispensed. They will be given a kit of patient education materials addressing the risks of BZDs and the benefits of reducing/stopping their use. This kit will be designed on the basis of patient education materials produced by the Canadian Deprescribing Society^1^ and adapted to the French context. The pharmacist will then plan with the patients 3 MIs to be carried out within the next 3 months. These interviews will last 30 to 60 min and will address the risks of using BZDR, as well as the benefits and modalities of stopping them. MI is a client-centered, semi-directive method for enhancing intrinsic motivation to change by exploring and resolving ambivalence (22). It is intended to work through four main principles: express empathy, support self-efficacy, roll with resistance, and develop discrepancy. During these interviews, the pharmacist will provide information about non-pharmacological ways to improve sleep or reduce anxiety, prevention of rebound phenomena, and will provide an example of de-escalation of doses (i.e., progressive reduction). The pharmacist will identify the patients’ representations of their medication and pathology (insomnia, anxiety), and will understand the barriers and facilitators for deprescribing. Any question the patients may have will be addressed. The choice to stop or reduce the dose of the BZDR will be the result of a shared medical decision (trio patient – GP – PC). To facilitate implementation, the pharmacists of the intervention arm will receive a 2-day specifically designed training course in MI by a certified organization prior to the intervention (Table 2). They will be given guidelines on the risks associated with BZDR, their deprescribing, and the management of patients who were deprescribed. If required, the pharmacists will be supported by the interventional public health department of the promoting center which will accompany them in their first MI. To avoid contamination, pharmacists working in pharmacies randomized in the control group will not be trained in MI and in deprescribing until after the study is completed.

**Table 2 tab2:** Objectives and program of the pharmacist’s training course in Motivational Interview.

Pedagogical objectives	
To discover Motivational Interviewing (MI) To become imbued with the spirit of the MI and to identify the corrective/repairing reflex To Mobilize the skills of the MI To use specific tools to share information in a motivational way To identify the change discourse To begin to focus questions and reflections to promote discourse-change To practice and receive feedback on MI practice in a training context	
Pedagogical means	
The training uses a variety of media (video, summary document, presentation, written exercises, workshops and oral role plays, brainstorming, exchanges between participants)	
Training program	
Day 0	Reading of a summary of MI: history, key elements of MI and definitions
Day 1	Creating the group dynamic – introduction to Engagement in MI Review of theory Ambivalence The corrective/repairing reflex Introduction to empathy and reflective listening Open questions Summarizing DDPD tool (motivational information sharing) Valuation Practice around a polycephalous interview (with several people) to building the alliance and engaging the relationship Conclusion
Day 2	Renewal of group dynamics and commitment The different types of simple and complex reflections Introduction to sustaining and changing discourses The different types of discourse-change Introduction to evocation strategies Observation of a live MI by the trainer on the subject of deprescribing BZDR Practice of a MI by each participant and feedback from the trainer with the elements congruent with the MI and one or two possible areas for improvement Conclusion and evaluation

#### Step 3: interprofessional communication

Following each interview, the pharmacist will inform the physician by means of a formalized report of the points discussed and of the relevant information concerning the objective of deprescribing (barriers, facilitators, etc.), using the patient’s comments when appropriate. The report will include the data collected from the patient during the interviews (expressed needs) as well as the pharmacist’s conduct (initiation of de-escalation, associated advice, dispensing of therapeutic alternatives). The pharmacist will inform the GP of the patient’s choice or not to get involved in a deprescribing process and of the protocol followed, if applicable. The objective of this exchange is to formalize the joint GP-CP intervention and to secure the deprescribing of BZDR for the patients.

Patients included in the control group clusters (non-interventional) will not benefit from the joint GP-CP intervention but will be managed in the usual way: medical consultation followed by dispensing of medication treatments. Blinding of participants for this type of intervention is not possible.

### Data sources and collection

The implementation outcomes will be measured by different procedures detailed below (see Outcomes section).

The sociological study will consider the variability of practice locations to be more representative: rural, urban, peri-urban. Depending on the location of the practice, the patient may have different social characteristics that will probably require professionals to adapt (vocabulary, arguments, conduct of the interview, etc.). Four days of observations will be conducted with pharmacists who have just been trained in MI to study, in action, how they conduct their first interviews with the older adults. These same pharmacists will be observed a second time at the end of the study, to see how their approach to MI has evolved.

A first wave of ten semi-structured interviews will be conducted with older adults who have already been seen by their pharmacist, to see what effects the pharmacist has had on their representations of BZDR and on their consumption.

Finally, three focus groups will be carried out, one with CPs, one with GPs and one with pairs. The first two will allow to identify any difficulties experienced in this interprofessional collaboration, but also what has been facilitated. The last focus group will allow the pairs to exchange and compare their point of view on multidisciplinary work and relevance of the collaboration.

Regarding the effectiveness of the intervention, the consumption of reimbursed drugs and the co-payments of the system will be assessed using the National Health Data System (SNDS) (23). This database provides access to all reimbursed healthcare, including drugs dispensed in pharmacies.

The outcomes concerning the clinical evolution of the patients will be measured using questionnaires administered to the patients by telephone by a clinical research associate.

## Data analysis

### Outcomes

#### Aim 1: implementation and effectiveness outcomes

Implementation outcomes will be assessed according to Proctor et al. classification (24) as described below: acceptability/adoption, appropriateness, cost and fidelity (Table 3). All qualitative data will be transcribed in full before being analyzed. The interviews and focus groups will be subject to thematic and structural discourse analysis. No software will be used.

**Table 3 tab3:** Implementation and effectiveness outcomes.

	General Practitioners and Community Pharmacists	Patients
Implementation outcomes		
Acceptability/Adoption	Nb of clusters included/Nb of clusters planned Reason for refusal	Nb of patients included/Nb of patients eligible Factors of receptivity
Appropriateness	GP & CP Sociological interviews CP Observations	Sociological interviews
Cost	Cost-Utility and Budgetary impact analysis	
Fidelity	Nb of clusters completing the study/Nb of clusters Rate of CP’s reporting to GP	Nb of appointments/Nb of planned appointments
	Nb, duration and frequency of MI	
Effectiveness outcome		
Medication		Cessation or reduction of BZDR at M12
Clinical		Patient reported outcomes

CP, Community Pharmacists; GP, General Practitioners; MI, Motivational interview; Nb, Number.

##### Acceptability/adoption

The achievement of the number of clusters and patients included planned in the protocol will be evaluated. A short questionnaire will be sent to a sample of GPs and pharmacists who refused to participate in order to understand the reasons for not participating in the study.

The patients’ factors of receptivity to the intervention (gender, age, couple, socio-economic level, last diploma, literacy level, frequency of consultations with the GP, duration of prescription, indications for BZDR) will be studied in order to identify a typical profile of the patient responding to the intervention.

##### Appropriateness

The sociological study will allow to analyze the appropriateness of this work in pairs on the deprescribing of BZDR among the older adults. We will study the impact of this collaboration on GPs and CPs, and in particular analyze the extent to which it allows for an increase in the competence of the professionals. Based on a field survey that will put the discourse (interviews) into perspective with the practices (observations), the effects of this arrangement on all parties and the effectiveness of this collaboration will be assessed, while identifying how each party has lived this experience, what they have learned and any resistance to change. In this way, how pharmacists use motivational interviews, how they conduct them, and what this multidisciplinary collaboration brings them will be studied, but also how they transmit new norms to the older adults and the concrete effects of these motivational interviews.

Furthermore, by observing the way in which these motivational interviews are constructed and conducted according to the different practitioners, and by putting these practices into perspective with the discourses of the doctors and pharmacists, we will be able to question the appropriateness of this multidisciplinary vision, and how it upsets the socialization and professional logics of the two.

##### Cost-utility

Economic efficiency of the implementation effort will be assessed following the HAS 2020 recommendations (25). A Cost-Utility Analysis (CUA) expressed as a cost per Quality Adjusted Life Year (QALY) will be performed from a collective perspective and with a time horizon of 12 months. The CUA will consider the direct costs of care from randomization to M12. Hospital and city care consumption data related to the management and its consequences will be collected in both arms via the Health Insurance database (SNDS). The data collected will include: medications, medical consultations, hospitalizations if applicable, and emergency room visits. A budgetary impact analysis from the point of view of the Health Insurance will be carried out following the CUA. It will be based on different scenarios of 5-year diffusion levels of the joint intervention.

##### Fidelity

The proportion of pairs completing the study, the proportion of patients who actually made appointments with the pharmacist, the number, duration and frequency of MI, and the rate of reporting made by the pharmacist to the GP will be measured through a logbook.

##### Effectiveness

The effectiveness will be assessed by the cessation or reduction of BZDR use at 12 months from inclusion. It will be described as the proportion of patients no longer being dispensed BZDR at 10 months after inclusion, with the last two months (10 to 12 months) not counted to account for possible residual BZDR use, or having decreased their average Daily Drug Dose (DDD) dispensing by 50%. The decrease will be calculated by comparing the average DDD dispense over the last 3 months of patient follow-up to the dispense observed during the 3 months prior to inclusion.

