### Study population and recruitment

#### Patients

In order to minimize the risk of subjective pre-selection of patients by the GP, a predefined list of eligible patients per cluster will be sent out to each GP by the Health Insurance according to the inclusion criteria detailed below, before randomization of the clusters and on the basis of the GP’s request. The study population will consist of patients aged 65 years and older, monthly users of at least one anxiolytic or hypnotic BZDR for more than 3 consecutive months (ATC classes N05BA, N05CD and N05CF). Patients meeting the eligibility criteria will be recruited by GPs during their medical encounters.

The inclusion criteria will be: outpatients aged 65 and over, followed by the GP and being delivered their medications by the pharmacist of the GP-CP pair, having a prescription for an anxiolytic or hypnotic BZDR prescribed at least 4 times in the past year, the last prescription being dispensed in less than 3 months and having been dispensed monthly during the last 3 months, affiliated to a social security scheme, and having given consent to participate in the research.

Non-inclusion criteria will be: patients living in an institution, participating in another clinical trial, with any medical condition that contraindicates BZDR discontinuation on the physician’s opinion, unable to participate in an interview or answer a questionnaire and with insufficient autonomy to carry out the steps inherent in the study. Patients living in an institution will be excluded because an unknown part of them have their BZDR not traced in the SNDS database (for administrative reasons), which could induce bias in our study.

If eligible, the patient will be offered to enroll in the study during a standard medical consultation. If he agrees to participate, signed informed consent will then be obtained, and the patient will be assigned a patient number automatically upon inclusion.

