### Statistical analysis

Variables measured at inclusion will be described according to the randomization group for all included patients. Quantitative variables will be described using the mean, standard deviation, quartiles and range. Qualitative variables will be described using the numbers and proportions for each modality.

In order to measure the impact of the intervention in real life, the analysis will focus on the intention-to-treat population: all patients included will be kept in the analysis sample according to their randomization group, regardless of protocol deviations.

For the effectiveness endpoint, a mixed logistic model will be built to study the proportion of deprescribing between MI condition (intervention) and usual care condition (control), and concomitantly accounting for the cluster effect associated with our design (28). For secondary analysis, the impact of the intervention on quality of life, anxiety disorders, sleep quality, dependence and autonomy will be estimated by comparing the EQ-5D-5L, GAD-7, ISI, ECAB, and IADL scores between the two groups using mixed models. As advocated by the literature (29), models will be adjusted on baseline covariates that are prognostic of the outcome, balanced or not at baseline, including *a minima* the following: age, sex, number of past attempts, suspected addiction. The impact of the intervention on hospitalizations and deprescribing failures will be estimated from hospitalizations (number of hospitalizations) and failures (number of discontinuations and then resumption).

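### The effectiveness endpoint, applied literally, counts patients who die or become untraced in SNDS before the outcome window as deprescribed

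*Protocol article*

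**What the plan says.** The Effectiveness paragraph (Data analysis, Outcomes, Aim 1) gives two routes to success. The first is cessation: "It will be described as the proportion of patients no longer being dispensed BZDR at 10 months after inclusion", with months 10 to 12 set aside for residual use. The second is reduction: "or having decreased their average Daily Drug Dose (DDD) dispensing by 50"%, obtained by "comparing the average DDD dispense over the last 3 months of patient follow-up to the dispense observed during the 3 months prior to inclusion".

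Under Data sources and collection, drug consumption is taken from SNDS: "This database provides access to all reimbursed healthcare, including drugs dispensed in pharmacies". Under Statistical analysis, the population is intention-to-treat: "all patients included will be kept in the analysis sample according to their randomization group, regardless of protocol deviations".

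Under Study population and recruitment (Patients), people living in an institution are not included because "an unknown part of them have their BZDR not traced in the SNDS database (for administrative reasons), which could induce bias in our study". This safeguard applies at entry only. The effectiveness definition does not mention death, institutional entry during follow-up, or time in hospital.

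**The concern.** The endpoint reads absence of a dispensing record as absence of use. That holds only while the patient is alive and while their drugs would appear in SNDS. The cohort is aged 65 and over and is followed for 12 months. The Background itself describes older BZDR users as more at risk of falls, dementia and death, and hospitalisation is a planned outcome. Some loss of dispensing unrelated to deprescribing is therefore foreseeable.

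The reason given for not including institution residents applies equally to someone who moves into an institution at month 5, but nothing carries it into follow-up. Under the stated definition such a patient is not missing data. The absent record satisfies the cessation criterion.

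Only 5% success is expected in the control arm, about 10 of 200 patients, so a handful of false successes is a large fraction of what is counted. Equal shares in both arms dilute the contrast. Unequal shares move the estimate in either direction.

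**Working it through.** **Inputs from Sample size and power:** control 5%, intervention 15%, alpha 5% (taken as two-sided), power 80%, intraclass correlation 0.05, 10 patients per pair, 20 pairs and 200 patients per arm.

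**Reproducing the plan.**
- Design effect = 1 + (10 − 1) × 0.05 = 1.45.
- Unpooled two-proportion formula: 138 per arm before clustering, and 138 × 1.45 = 200.1. This matches the stated 200. The pooled version gives 141 × 1.45 = 204.5.
- Effective size per arm = 200 / 1.45 = 137.9.
- Power at 200 per arm: 80.2% (unpooled) or 79.4% (pooled).

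The sample size is correct on its own inputs.

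**Adding misclassified patients.** Let q be the share of an arm counted as deprescribed only because dispensing is no longer observed. The article does not give q; it is an assumption, shown over a range and first taken as equal in both arms. If the planned rate p describes the remaining patients, the counted rate is p(1 − q) + q. Unpooled power = Φ(difference / SE − 1.96), where SE² = [p₁(1 − p₁) + p₂(1 − p₂)] / 137.9 and p₁, p₂ are the counted rates.

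| q | False successes per arm (200q) | Counted control | Counted intervention | Odds ratio | Power, pooled to unpooled |
|---|---|---|---|---|---|
| 0 | 0 | 5.00% | 15.00% | 3.35 | 79–80% |
| 1% | 2 | 5.95% | 15.85% | 2.98 | 75–76% |
| 3% | 6 | 7.85% | 17.55% | 2.50 | 68–69% |
| 5% | 10 | 9.75% | 19.25% | 2.21 | 61–62% |

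At q = 5%, 0.05 / 0.0975 = 51% of counted control successes would be artefact.

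**How much is due to the rule rather than the events?** With the same 5% of patients affected, counting them as non-success gives 77% power (pooled) and excluding them gives 78%. Most of the loss at q = 5% therefore comes from counting them as success.

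**Unequal shares, true difference 10 points.**
- 3% control, 5% intervention: 19.25% − 7.85% = 11.4 points.
- 5% control, 3% intervention: 17.55% − 9.75% = 7.8 points, power 47% (pooled).

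**The case against.** The strongest reply is that this is a condensed article. The coding of deaths and institutional entries is often left to the full protocol or analysis plan, and neither is shown. No sentence says that such patients are successes, the stated aim is cessation or reduction of use, and the intention-to-treat sentence says who is analysed, not how they are coded. It is right that a fuller document may contain a rule, and the authors probably do not intend to count deaths as success. But the point does not rest on missing detail. The definition is given, it classifies these patients, and the article names the tracing bias and then deals with it only at baseline.

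Other parts of the reply limit the point and stand:
- A reader might infer that everyone who enters an institution disappears from SNDS. The article says only that an unknown part is untraced.
- A reader might infer that any long hospital stay creates a false success. It does so only if it covers the window used. That inpatient drugs are absent from the dispensing data is itself an inference.
- A reader might infer that tying the reduction criterion to the end of each patient's follow-up adds false successes. For someone who dies or leaves early, that window can fall before the event, while dispensing is still recorded. The cessation route carries the problem, and because the two routes are alternatives it is sufficient alone.
- The 5% control rate is said to reflect current trend, without its basis. If it came from dispensing data it may already contain such losses, and adding q would count them twice.
- Non-inclusion of institution residents and of patients with insufficient autonomy should keep q down.

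**Conclusion.** The point holds in a limited form. Applied literally, the rule counts as deprescribed patients who die before the outcome window, the untraced part of those who enter an institution, and patients whose hospital stay covers the window.

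The size is unknown. The figures of 75–76%, 68–69% and 61–62% power at q = 1%, 3% and 5% assume that q is the share actually misclassified, that it is equal in both arms, and that the planned 5% excludes these events. If the planned 5% and 15% are already on the counted scale, the loss of power against plan disappears, but the endpoint still mixes deprescribing with death and loss of tracing.

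Two stronger conclusions are not supported. One is that a few percent of such patients doubles the control rate: at q = 3% it rises from 5% to 7.85%, and near-doubling needs about 5%. The other is that harm in one arm will appear as benefit. Unequal shares would bias the effect, but nothing in the article indicates that the shares will differ or in which direction.

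**What to change.** Amend the Effectiveness definition, and the analysis plan to match:

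1. Count success only if the patient is alive and observable in SNDS, not living in an institution, throughout the outcome window.
2. Class death or institutional entry before the end of that window as non-success in the primary analysis, with a sensitivity analysis excluding these patients.
3. Anchor the 3-month dose window to a fixed time from inclusion instead of the end of each patient's follow-up.
4. Report deaths and institutional entries by arm.

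If another rule for death is preferred, it should be stated before outcome data are seen. The choice between non-success and exclusion costs little power (77% against 78% at 5% affected).

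The change costs wording and one status variable, and no extra patients. Vital and residence status must be obtained from the GP, the pharmacist, telephone contact or SNDS. The article does not say that SNDS supplies it, and Table 1 appears to end the questionnaires in March 2024 although enrolment runs to December 2023, so the planned calls may not reach month 12 for every patient. A small downside is that some patients who truly stopped and later died or entered an institution will count as non-success.
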